## Abstract

**Background:**

Shortening the standard 6-month treatment for drug-susceptible pulmonary tuberculosis (DS-PTB) would be a major improvement for TB case management and disease control.

**Methods:**

We are conducting a randomized, open-label, controlled, non-inferiority trial involving patients with smear-positive, newly diagnosed DS-PTB cases nationwide to assess the efficacy and safety of two 4.5- month regimens in comparison to the standard 6-month WHO recommended regimen. The regimen used in one experiment group is a 4.5-month fluoroquinolone-containing regimen, which consists of full course of levofloxacin, isoniazid (H), rifampin (R), parazinamid (Z) and ethambutol (E). Regimen used in the second experiment group includes 4.5-month full course of H, R, Z, E with levofloxacin removed. Patients in the control group, receive H, R, Z and E for 2 months, followed by 4 months of H and R. The primary endpoint is treatment failure or relapse within 24 month after treatment completion.

**Discussion:**

Results from this trial along with other studies will contribute to the science of constructing a shorter, effective and safe regiment for TB patients.

**Trial registration:**

The protocol has been registered on ClinicalTrials.gov on 2 September,2016 with identifier NCT02901288.

## Background

Tuberculosis (TB) is now the leading infectious disease killer worldwide. In 2015, there were an estimated 10.4 million new TB cases worldwide. China is one of 30 TB high burden countries with third largest TB population globally. In 2015, 0.9 million new cases were estimated with an incidence of 67/100,000, accounting for 8.7% of the global total [1, 2]. Currently, 6-month short course remains the standard of care for the treatment of drug-susceptible pulmonary TB (DS-PTB), and its efficacy has been evaluated and established in controlled trials. Although standard 6-month regimens for drug- susceptible TB are highly efficacious, the duration of treatment is still considerably longer than that of most of respiratory infections. Poor adherence leads to treatment failure which in turn drives the emergence of drug resistance. Shortened treatment for DS-PTB would improve treatment outcomes and reduce costs. So regimens for TB that are shorter and/or simpler than the current 6-month regimen are needed.

The effectiveness of fluoroquinolones (FQ) in vitro, their sterilizing effect in both mice and human in vivo and their success in treating multi-drug resistant TB(MDR-TB) raised hope that if used as first line drugs [3–6], they might contribute to shortening therapy duration of DS-PTB. In 2014, 3 independent clinical trials named REMoxTB, RIFAQUIN and OFLOTUB/Gatifloxacin (Gfx) simultaneously reported final results of shortening treatment duration for DS-PTB by using FQ-based regimens [7–9]. Unfortunately, noninferiority for these regimens was not shown as compared to the standard 6-month regimen, indicating that shortening treatment to 4 months was not effective in these settings. Challenges as we faced, optimizing regimens for DS-PTB with shorter duration are still promising. The first pharmacodynamic data showed that levofloxacin(Lfx) was less effective than moxifloxacin(Mfx) and Gfx. Lfx was given at a dose less than 500 mg/day in these early studies [10]. With the prescription increase at the dose of 1000 mg/day in recent studies, Lfx showed the best early bactericidal activity as active as Mfx at 400 mg during the first 7 days of treatment [3]. Other studies have also shown that Mfx and Gfx are better than ofloxacin, but do not contain comparison with Lfx [11]. It seems to reveal that Lfx at high doses, rather than low doses, has better pharmacodynamic qualities than either Mfx or Gfx. Additionally, Lfx is less expensive, more widely available, and may be less likely to prolong the QT interval compared to later generation of FQs. Previous study showed that Z inhibited the ribosome-sparing process of trans-translation. Trans-translation is essential for freeing scarce ribosomes in nonreplicating organisms. Therefore, Z could eradicate persisting organisms which are the major cause of recurrence of TB [12]. If Z is given during the whole course, it can improve the sterilizing activities against *mycobacterial tuberculosis* (MTB) and reduce relapse of TB. On the basis of the supportive evidence, a multicenter randomized controlled clinical trial is currently in progress to evaluate whether 4.5 months of an Lfx-containing regimen will be as effective as 6 months of the standard regimen for the treatment of DS-PTB. Meanwhile, given the strong bactericidal and sterilizing activities of H, R, E and Z, parallel treatment shortening trial is also in progress with the consideration of increasing drug combination at continuation phase as compared with the standard 6-month regimen.

To our knowledge, preferable dosage and treatment duration of Lfx’s contribution combined with first line anti-TB drugs is not well studied. Neither is the shortening regimen with full length of treatment using H and R. This study aims to assess the efficacy and safety of 2 shortened regimens (study regimens) for DS-PTB compared to the WHO standardized 6-month regimen (control regimen). Success of the ultra-short course TB regimens would further shorten the treatment duration of DS-PTB, improve compliance and cure rates, reduce rates of adverse reactions and cost, as well as minimize the risk of drug resistance.

## Methods and Design

### Study design and oversight

We did a multicenter, randomized, controlled, open-label clinical trial within the framework of the China Tuberculosis Clinical Trial Consortium (CTCTC). The trial was sponsored by Ministry of Science and Technology of the People’s Republic of China and implemented by the leadership of Beijing Chest Hospital, Capital Medical University, together with other 34 TB specialized hospitals or Centers for TB Control and Prevention nationwide. The study protocol, the patient information sheets and consent forms were reviewed and approved by Central Ethics Committee of Beijing Chest Hospital, Capital Medical University/Beijing Tuberculosis and Thoracic Tumor Research Institute and the other participating medical facilities all approved the decision. The data and safety monitoring board planned to review efficacy and safety data at intervals of approximately 3 months throughout the study. Some of the trial medications were donated by Daiichi Sankyo Company Limited and Chengdu Jinhua Pharmaceutical Co.Ltd., but neither of these companies had any role in the study design, data accrual or further data analysis.

### Study patients

Adult patients who are newly diagnosed, previously untreated or treated less than 1 month with anti-TB drugs, are determined by chest X-ray with any abnormality consistent with TB and positive results of sputum smears on two occasions, with culture-confirmed susceptibility to H, R, E and Z and Lfx. All patients with written or witnessed oral informed consent were recruited if they met the trial eligibility criteria at screening. Detailed inclusion and exclusion criteria is provided in Table 1.

**Table 1 Tab1:** Eligibility criteria

Inclusion criteria	Exclusion criteria
Is willing and able to give informed consent to participate in the trial treatment and follow-up (signed or witnessed consent if the patient is illiterate)	Is HIV positive
Is aged of 18–65 years old	Is concomitant with mental disorders
Is previously untreated or treated less than 1 month with anti-TB drugs	Is concomitant with diabetes while mellitus blood glucose out of control
Has 2 positive sputum smear results for mycobacterium TB at screening	Is pregnant or breastfeeding
Has a chest X-ray abnormality compatible with a diagnosis of PTB	Has a prolonged QTcF^a^ (>480 ms)
Is not pregnant for female patient at bearing age and willing to use effective contraception during study period	Is currently participate in another trial of a medicinal product
Has CrCl^b^ > 30 ml/ min, HB^c^ > 7.0 g/dL and PLT^d^ > 50 × 10^9^/L at screening	Is concomitant with severe cardiovascular, hepatic, renal, nervous system, hematopoietic system injury and other diseases, or concomitant with neoplastic diseases
Has ALT^e^ and TBIL^f^ less than 2 times the upper limit of normal at screening	Has extensive lesion in the lung concomitant with respiratory insufficiency
	Has known allergy to any of the anti-TB drugs in the trial
	Is taking any medications contraindicated with the medicines in any trial regimen of the study

^a^
*QTcF* Fridericia-corrected QT, ^b^
*CrCl* creatinine clearance, ^c^
*HB* hemoglobin, ^*d*^
*PLT* Platelet, ^e^
*ALT* alanine aminotransferase, ^f^
*TBIL* total bilirubin

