### Sample size assumption

Under the conditions of the trial, we assumed that the standard 6-month regimen has a 95% or higher sputum culture conversion rate and with estimated 92.5% of that for 4.5-month study regimen based on the published data. The study was designed to determine whether either of the shortened study regimens was not inferior to the control regimen and a margin of noninferiority of 5% was used. With the assumption that as many as 20% of patients will loss to follow-up or not be assessable in the primary analysis, and with the consideration of approximately 5.5% primary drug resistance prevalence, a total target sample size was 3900 patients (1300 subjects per group) would be required to demonstrate noninferiority, with a statistical power of 0.8 and an alpha level of 0.05 (one-sided). Participant recruitment began in August 2016 and is expected to finish in December 2018.

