### Outcome measures

The primary efficacy outcome measures include the percentage of participants with treatment failure or relapse by 24 months after the end of treatment, percentage of participants with treatment failure at either 4.5 months or 6 months after randomization. The secondary efficacy and safety outcomes include the time to sputum (both smear and culture) conversion within intensive phase of 2 months and the percentage of participants with sputum conversion (both smear and culture) at the completion of treatment, the number of adverse reactions occurring on treatment and during the follow-up period, adherence to treatment and radiological manifestation transition. Of note, treatment failure was defined as sputum smear positive at the end of treatment and relapse after completion of treatment is defined as at least one positive culture in the scheduled follow-up visits in two years. Participants with negative cultures at the end of follow-up are considered to have had a favorable outcome. For all treatment failures and relapses, one culture of a sputum sample obtained before treatment and one culture of a sputum sample obtained after treatment failure or relapse are planned to store at −80 °C and the samples will be sent to national clinical TB reference lab in Beijing Chest Hospital for further research. The detailed observation schedule is present in Table 3.

**Table 3 Tab3:** Assessment schedule – for all patients recruited

Observation/Investigation		Screening	Treatment Phase (weeks)									Follow-up (Post-treatment phase, months)							
Study visits		0	2	4	6	8	12	16	19	22	26	3	6	9	12	15	18	21	24
Time window (days)			±3	±3	±3	±3	±7	±7	±7	±7	±7	±14	±14	±14	±14	±14	±14	±14	±14
Demographics		X																	
Written or witnessed informed consent		X																	
Patients eligible criteria judgement		X																	
Medical history and clinical assessment		X	X	X	X	X	X	X	X	X	X	X	X	X	X	X	X	X	X
Concomitant diseases and medication taken assessment		X	X	X	X	X	X	X	X	X	X	X	X	X	X	X	X	X	X
Randomized assignment		X																	
Efficacy evaluation																			
Bacteriological test	Sputum smear	X	X	X	X	X	X	X	X	X	X	X	X	X	X	X	X	X	X
	Sputum culture	X	X	X	X	X	X	X	X	X	X	X	X	X	X	X	X	X	X
X-ray		X				X			X		X		X		X		X		X
Safety evaluation																			
Complete blood count		X		X		X	X	X	X	X	X								
Urinalysis		X		X		X	X	X	X	X	X								
Hepatic and renal functions		X		X		X	X	X	X	X	X								

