Since Lfx administered with high dose is of comparable efficacy compared with Mfx and Gfx against MTB, it is possible to introduce Lfx to the regimen for shorter duration of DS-PTB. However, there is also concern that Lfx may fail as first-line anti-TB drugs because of its widely applied for common infections such as urinary and gastrointestinal tracts, wounds, and other lung infections. In high-TB-burden countries, a great number of cases with undiagnosed TB are likely to take an FQ, which could be selected for resistance in at least a fraction of MTB they harbor [23]. Several studies focus on FQ resistance and its association with previous FQ exposure indicated a low prevalence. Researchers from Korea found 2.6% FQ resistance in patients exposed to FQs while 3.4% resistance in patients without FQ exposure [24]. A study from Taiwan found no correlation of FQ resistance with either FQ exposure or duration of FQ exposure, but saw a positive correlation with previous anti-TB treatment and resistance to any other drugs [25]. Previous study from the same research team comparing sputum taken both before and after a course of FQs treatment showed that patients who received an FQ before standard anti-TB treatment had a poor prognosis, most likely as a result of the emergence of drug resistant. 11.1% of the MTB obtained FQ resistance after taking an FQ for 1–3 weeks [26]. The fifth national TB epidemiology survey in China of 2010 reported that Lfx resistant TB accounted for 9.1% among new TB patients [27]. A high prevalence of FQ-resistant TB may void the possibility of Lfx as first line drug for shortening DS-PTB treatment duration. Appropriate bacteriological and histopathological tests for TB should be performed as early as possible before Lfx-containing regimen is recommended. If the study regimen is successful, it is expected to provide a new standard of care for DS-PTB which would cut down the number of required clinic visits and the burden on the health care system and could also decrease the percentage of patients who fail to complete the full course of current longer therapy. If the study regimens are shown to be noninferior or superior to the control regimen, that would represent an even greater advance for patients with DS-PTB and TB control programmes globally. However, there are a few negative aspects that need to be considered before an FQ-containing first-line regimen could be broadly recommended. The FQs are fairly effective drugs for common nonspecific respiratory syndromes and community-acquired pneumonia, and curtailing this usage to ensure they remain effective as first-line TB drugs may not prove beneficial to all-cause morbidity and mortality at the community level. Also, using FQs as standard first-line therapy would reduce their effectiveness against MDR-TB, and could perhaps result in the emergence of more XDR-TB. Its implementation might be suggested only where the prevalence of Lfx-resistant TB is low and FQs are not routinely used for nonspecific respiratory symptoms when TB cannot be effectively excluded would reduce concerns above.

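### Susceptibility to five drugs is an entry condition in the text, but the criteria table and schedule let patients be randomised without it, and the 5.5% resistance allowance does not match the five-drug rule

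*Protocol article*

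**What the plan says.** All references are to the protocol article.

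- **Study patients, text.** Participants are smear-positive adults "with culture-confirmed susceptibility to H, R, E and Z and Lfx". The next sentence says that consenting patients "were recruited if they met the trial eligibility criteria at screening".
- **Study patients, Table 1.** The text introduces the table with "Detailed inclusion and exclusion criteria is provided in Table 1". Its only bacteriological row is "Has 2 positive sputum smear results for mycobacterium TB at screening". No inclusion or exclusion row mentions culture, susceptibility or resistance.
- **Outcome measures, Table 3.** The row "Randomized assignment" has a single mark, in the Screening column (visit 0). The eligibility judgement and the first sputum culture are marked in the same column. There is no earlier visit and no row for susceptibility testing.
- **Sample size assumption.** The target of 3900 (1300 per group) is meant to absorb up to 20% lost or unassessable. It is also set "with the consideration of approximately 5.5% primary drug resistance prevalence". The drug or drugs behind the 5.5% are not named.
- **Discussion.** A 2010 national survey is cited as showing that "Lfx resistant TB accounted for 9.1% among new TB patients".

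**The concern.** The four design statements cannot all be followed. If susceptibility to five drugs must be confirmed before entry, Table 1 omits a criterion that decides eligibility, Table 3 leaves no step at which it could be checked, and a per-group resistance allowance has no purpose. If patients enter on smear and X-ray, as the tables imply, the text misstates who is enrolled.

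Two things are at stake. The first is who gets randomised: sites reading the text and sites reading the tables would admit different patients to a trial whose target is drug-susceptible disease. The second is the size of the allowance. If patients with resistant isolates are to be set aside, the number lost depends on the drug list. The text's list includes levofloxacin, for which the article itself quotes a prevalence above the whole allowance.

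**Working it through.** **Step 1. The statements side by side**

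| Place | Is susceptibility needed before randomisation? |
|---|---|
| Study patients, text | Yes, to H, R, E, Z and Lfx, with eligibility judged at screening |
| Table 1 | Not asked for |
| Table 3 | First culture and randomisation in the same column; no susceptibility row |
| Sample size assumption | Implies no: resistant patients are allowed for |

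The last row follows because the target is stated per randomised group. A patient excluded for resistance before randomisation never joins a group, so no per-group allowance would be needed.

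**Step 2. The allowance against the article's own prevalence**

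If patients enter on smear, the expected numbers with resistance are:

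- at 5.5%: 3900 × 0.055 = 214.5, about 215 (about 72 per arm)
- at 9.1%: 3900 × 0.091 = 354.9, about 355 (about 118 per arm)

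Resistance to any of five drugs cannot be rarer than resistance to levofloxacin alone. So if the survey figure applies to this population, 9.1% is a lower bound for a five-drug rule.

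**Step 3. The stated sample size**

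Inputs from Sample size assumption: control 95%, experimental 92.5%, margin 5 points, one-sided alpha 0.05, power 0.80. With unpooled variance:

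n = (1.645 + 0.842)² × (0.95×0.05 + 0.925×0.075) / (0.05 − 0.025)² = 6.183 × 0.116875 / 0.000625, about 1157 assessable per arm.

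- 20% loss only: 1157 / 0.8 = 1447 per arm
- 20% loss and 5.5% removed: 1157 / (0.8 × 0.945) = 1531 per arm
- 20% loss and 9.1% removed: 1157 / (0.8 × 0.909) = 1592 per arm

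The stated 1300 is not reproduced by these or by the other standard inflations tried (additive, multiplicative, continuity-corrected, one-sided 0.025). The nearest is a non-standard variant: the control variance in both arms gives 940, and 940 / 0.745 = 1262. This mismatch is a separate matter, but it means the power must be computed forwards from 1300.

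**Step 4. Power with 1300 per arm**

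Power = Φ(0.025 / √(0.116875 / n) − 1.645), where n is the number assessable per arm.

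| Removed for resistance | n per arm | Power |
|---|---|---|
| None (20% loss only) | 1300 × 0.8 = 1040 | 76.2% |
| 5.5% | 1300 × 0.8 × 0.945 = 983 | 74.1% |
| 9.1% | 1300 × 0.8 × 0.909 = 945 | 72.7% |

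Adding the 20% and 5.5% instead of compounding them gives 1300 × 0.745 = 968.5 and 73.6%. If the 5.5% covered only the other drugs and were independent of levofloxacin resistance, n would be 1300 × 0.8 × 0.945 × 0.909 = 893 and power about 71%. The documents do not say whether that is so.

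**The case against.** The strongest reply is that the intended design is easy to guess: randomise on smear, then drop patients whose baseline isolate proves resistant. That fits the 5.5% allowance and a modified intention-to-treat population. The exact definition of that population may sit in the full protocol or the analysis plan, which are not shown. This stands in part. The absence of a population definition from an article is no finding, and uniform removal by baseline isolate would still estimate the effect in drug-susceptible disease. But the article does not describe that design. It words susceptibility as a feature of enrolled patients judged at screening, and a population definition elsewhere cannot settle which entry rule sites follow.

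A second reply is that Table 3 gives no length for Screening and that up to a month of earlier treatment is allowed, so a culture or susceptibility test might already be under way. That is possible, and the timing argument is an inference to that extent. It does not explain why the detailed list omits the criterion, or why resistant patients are allowed for per group.

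A reader might go further and infer a biased comparison: resistant patients kept in and diluting a true difference, or levofloxacin-resistant patients removed only from the levofloxacin arm. The documents do not support either. Nothing in them points to removal that differs by arm. Two of the three arms contain no levofloxacin, so resistance to that drug alone gives no reason to expect excess failure there. No outcome rates for resistant patients are given from which a bias could be computed.

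**Conclusion.** The contradiction stands on the article's own text: the eligibility prose conflicts with Table 1, Table 3 and the resistance allowance on who may be randomised. It does not depend on any calculation.

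The allowance is also inconsistent with the stated rule, since 5.5% is less than the 9.1% quoted for one of the five drugs. This rests on the 2010 survey figure applying to the trial's patients, which the article does not establish.

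The effect on power is modest. Going from no resistance exclusion to 5.5% costs about 2 points (76.2% to 74.1%), and going on to 9.1% costs a little over 1 more (to 72.7%). Most of the gap from 80% is there before any resistance exclusion and should not be put down to this point. These figures assume the article's 95% and 92.5% rates, unpooled variance, and resistance losses that come on top of the 20% and compound with it.

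The documents do not support a claim that the primary comparison is biased, or that it must miss its target population.

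**What to change.** 1. Make the Study patients text, Table 1 and Table 3 agree. If susceptibility is required before randomisation, add it to Table 1 and show in Table 3 when the result is obtained.
2. If randomisation comes before the results, say so, and reword susceptibility as a post-randomisation exclusion from analysis. Base it only on the isolate taken before randomisation, use the same drug list in all three arms, and apply it without knowledge of arm or outcome.
3. Name the drugs behind the allowance in Sample size assumption, set its size from the same list as the exclusion rule, reconcile it with the 9.1% in the Discussion, and restate the power.
4. Reconcile how patients found resistant after randomisation are managed with the regimens as described. This review takes no position on what that management should be.

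The cost is wording in the eligibility text, two tables and the sample size paragraph. The downside is a less favourable stated power: about 73% to 74% with 1300 per arm, not 80%.

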### Randomization and study regimens

Eligible patients who have provided written or witnessed oral informed consent were randomly assigned a unique study number sequentially on a web-based computerized algorithm, with the use of blocks of variable sizes which were stratified according to the study sites. Patients were randomized in a ratio of 1:1:1 to one of three regimens: a control regimen 2HREZ/4HR, which consists of 6 months of H and R administered daily, supplemented by E and Z in the first 2 months; a 4.5-month Lfx-containing regimen 4.5LfxHREZ, which is composed of H, E, Lfx, R, and Z administered daily, throughout the length of therapy; and another 4.5-month regimen4.5HREZ with Lfx removal from the former regimen. In all three groups, drug doses were adjusted according to patient’ weight, as described in Table 2. Treatment is directly observed at each local health facility and supervised by patient-friendly App management tools.

**Table 2 Tab2:** Anti-TB drugs and their dosage used in the trial

Drugs (Abbreviation)	Formulation	Dosage Daily	
		<50 kg	≥ 50 kg
Isoniazid (H)	100 mg/tablet	300 mg	300 mg
Rifampicin (R)	150 mg/ tablet	450 mg	600 mg
Ethambutol (E)	250 mg/ tablet	750 mg	1000 mg
Pyrazinamid (Z)	250 mg/ tablet	1500 mg	30 mg/kg
Levofloxacin (Lfx)	100 mg/ tablet	600 mg	800 mg

